## Background

Total knee arthroplasty (TKA) is the only effective treatment for end-stage symptomatic knee damage caused by osteoarthritis or rheumatic arthritis. There is a trend towards younger and more active patients who receive a TKA, making higher demands towards their implant. Furthermore, a considerable share of (younger) TKA patients is overweight or obese [1, 2]. Higher activity levels and higher patient weight induce higher loads on the prosthesis components, especially on the meniscal component, which serves as gliding surface for articulation of the femoral component. Increased loads on the gliding surface may result in wear of the device material, leading to debris and aseptic loosening [3, 4]. This emphasizes the importance of the material properties on the outcome of TKA. After its introduction in the early 1960s, ultra-high molecular-weight polyethylene (UHMWPE) has represented the material of choice for the gliding surface [3]. Research on UHMWPE aimed to improve material properties and wear resistance. Improvements regarding wear resistance were achieved by crosslinking of UHMWPE through ionizing radiation. However, this process induces formation of free radicals in the material, which after contact with oxygen leads to oxidative degeneration, material embrittlement, and impairment of mechanical properties [5]. Remelting and annealing were introduced as post-irradiation treatments to improve oxidative stability of the material, but negative effects were induced by these treatments regarding mechanical properties [6]. Therefore, a method to prevent oxidation of crosslinked UHMWPE without modifying mechanical properties was searched for.

Vitamin E is an effective natural antioxidant, occurring in cell membranes and preventing phospholipids from being oxidized by free radicals [7]. Similarly, vitamin E prevents UHMWPE from irradiation-induced oxidation [8] and therefore represents a promising stabilizer of crosslinked UHMWPE. Two methods are deployed for supplementation of UHMWPE with vitamin E: blending, where the raw material is mixed with vitamin E powder before the irradiation and cross-linking process; and doping, where the irradiated implant is doped with vitamin E. Biomechanical data indicated that vitamin E-enriched crosslinked UHMWPE has an advantageous oxidation profile (also after aging) while maintaining mechanical properties important for the gliding surface of a TKA [9, 10, 8, 11].

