#### Secondary endpoints and measures

The following secondary endpoints will be measured to evaluate the safety and performance of the investigational devices.

Preoperatively, data regarding demographics and anamnesis such as age, gender, weight, height, primary diagnosis, concurrent conditions, other joint restrictions, and ASA status will be collected and documented. Intraoperative and surgery-related data (e.g., duration of surgery, anesthesia, blood loss, length of hospital stay, used implant components incl. coating, and intraoperative complications) will also be collected and documented.

Survival of the implant (components) will be analyzed by Kaplan–Meier Analysis [30]. Survival in the sense of this study is defined as removal or exchange of any primary implant component including the removal or exchange of the meniscus component. Secondary interventions at the index knee, e.g., secondary patella replacement, do not count as a revision if no further exchange of the former implant components occur.

Clinical outcome will also be measured with the Oxford Knee Score (OKS), a 12-item, patient-reported questionnaire originally developed and validated specifically to assess function and pain in patients undergoing TKA. It is short, reproducible, valid, and sensitive to clinically important changes over time. OKS ranges from 0 to 48 with 48 being the best outcome [31].

Quality of life of the patients will be analyzed using the 5-dimension 5-level measure of the EuroQol Group (EQ-5D-5L), which is a simple and generic measure for clinical and economic assessment. The questionnaire covers five different dimensions (mobility, self-care, usual activities, pain/discomfort, anxiety/depression) rated in 5 levels (from “the worst health you can imagine” to “the best health you can imagine”) [32]. The questionnaire is filled by the patients themselves.

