Radiographic evaluation will be used to evaluate the implant status as well as device condition and potential presence of device-related adverse events including fracture, wear, loosening, or radiolucencies. An external x-ray laboratory will perform the analysis and evaluation of radiographs. In particular, radiolucencies at the interface between the implant and bone, migration of the femur and tibia component in relation to the bone, femoral-tibial angle, mechanical lateral femoral angle, and mechanical medial tibial angle will be analyzed. Furthermore, a new method combining 2-dimensional–3-dimensional registration and artificial intelligence will be applied, which enables accurate determination of changes in the postoperative polyethylene wear in situ. The precision and accuracy of this method is comparable to radiostereometric analysis [33].

Oxidation profile and wear analysis of available retrievals will be analyzed by the biomechanical laboratory of the sponsor. Special focus of these analyses is the oxidation profile, the wear behavior, the mechanics, and the cumulative linear abrasion of these retrievals. These measurements will provide in vivo data regarding the implant material in addition to detailed in vitro data already available [34, 35, 11].

During the course of the study, any upcoming intraoperative or postoperative (serious) adverse device events or effects related or not related to the product under investigation will be documented. The total number of adverse events will be summarized and further evaluated by the sponsor and reported according to local legislation and necessity. Recorded complications will be categorized and analyzed to assess the safety of the investigational product.

In case a patient requires revision of the primary implanted knee endoprosthesis, additional information on the revision surgery will be collected. The reason for revision together with the clinical symptoms shall be documented. Further examinations (e.g., arthroscopy) prior to the revision and the date of revision surgery will be documented. If pre-revision radiographs are taken as part of the clinical routine, the results of the radiographic analysis will be documented.

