**Table 1 Tab1:**
[figure not shown]
Data acquisition during the course of the study

^*^Required images: knee AP (standing), knee lateral (standing)

^**^Additionally: long leg (standing)

(X): radiographic evaluation may be performed at either visit

There are no specific plans to promote participant retention and complete follow-up. The patients are informed about the follow-up visits before their decision to participate in the study. The visits are kept to a minimum (3 months, 12 months, 5 years, 10 years) and accord to typical follow-up examinations also performed in non-study patients. In addition, patients will receive the OKS self-assessment score at 3 and 7 years postoperatively, to reduce loss-to follow-up rate and allow better monitoring of study patients. Patients will be requested to send the OKS questionnaire back to the study center.

Reasonable effort should be made by the study centers to contact any patient lost to follow-up during the course of the study in order to complete assessments and retrieve any outstanding data and study supplies.

The final programming will be performed after closure of the database by use of an appropriate statistical software package SAS. The sponsor has an overview of results from all participating centers. All data will be analyzed by means of appropriate tables, figures, listings, and statistical tests. Missing data will be analyzed as such and will not be replaced by estimates. The statistical analysis of the primary endpoint has a confirmative character, whereas the secondary endpoints will be analyzed explorative. This must be considered when interpreting the *p*-values and confidence intervals. The description of the patient cohort in means of demographic data and the baseline values of investigated parameters will take place as whole as well as grouped by the therapy group. Analyses will be performed according to the intent-to-treat principle. The consistency of the results will be tested by per-protocol analysis (sensitivity analysis).

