The study hypothesis will be tested using a two-sample *t* test. The results of the KSS Score will be analyzed as sum of the sub scores fKSS and kKSS. Primary testing will be done comparing the MXE with the β-PE group. Comparison between the different implant types might be done exploratively. Each implant variation (UC Pro vs. PS Pro) will be tested individually for primary endpoint analysis. Secondary endpoints will be tabulated as frequencies and rates/results respectively as means and standard deviations. Confidence intervals will be used when appropriate.

An explorative interim analysis of secondary objectives will be done 1 and 5 years postoperatively. It is intended to publish the 1-year as well as the 5- and 10-year results in a peer-reviewed journal in order to contribute to publicly available knowledge. Furthermore, the study and (intermediate) results may be presented on scientific conferences. Therefore, data of all available patients and centers shall be included. Manuscripts shall be reviewed and approved by all participating study centers. In case that the study results cannot be published in a peer-reviewed journal (e.g., due to non-significant results), a manuscript shall be deposited in a preprint archive. Furthermore, a study report will be attached to the ClinicalTrials.gov entry of this study.

Authorized, qualified representatives of the sponsor or designated personnel of a contract research organization will perform monitoring visits at investigational sites in regular intervals to verify adherence to protocol and local legal requirements, to perform source data verification and to assist the investigator in study related activities. Approximately one visit per site and year is planned, with more visits in the beginning of the study. As a risk-based approach, discovered deviations from the study protocol may increase the number or intensity of monitoring visits. Site audits are not generally planned. If monitoring activities reveal the necessity, e.g., due to severe deviations from GCP principles, site audits may be performed.

Vendors employed for the study were audited and approved by the processes of the sponsor supplier quality management.

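### No stated rule covers knees revised before a film visit, so the 5- and 10-year radiographic tables would describe mainly unrevised knees and understate loosening

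*Protocol article*

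**What the plan says.** The Background names the harm at issue for the gliding surface: "Increased loads on the gliding surface may result in wear of the device material, leading to debris and aseptic loosening". Under Secondary endpoints and measures, radiographs are read for the "potential presence of device-related adverse events including fracture, wear, loosening, or radiolucencies", together with migration and in-situ polyethylene wear. An external laboratory does this, and Randomization and blinding says the reading is blinded.

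The section on data collection and statistical analysis fixes the summary: "Secondary endpoints will be tabulated as frequencies and rates/results respectively as means and standard deviations". It adds: "Missing data will be analyzed as such and will not be replaced by estimates". Analyses follow intent-to-treat, with a per-protocol sensitivity analysis.

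One time-to-event analysis is named: "Survival of the implant (components) will be analyzed by Kaplan–Meier Analysis". Its event is removal or exchange of any primary component, the meniscus component included, whatever the cause. For revised knees the reason is documented, and "If pre-revision radiographs are taken as part of the clinical routine, the results of the radiographic analysis will be documented". Complications are categorized and analyzed, and wear is measured on available retrievals. No sentence says how a knee revised before a film visit is handled in the radiographic summaries.

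**The concern.** A knee with serious loosening or wear may be revised before its next scheduled film. It then has no later film of the original components, or it has a film of components put in afterwards. Neither describes the allocated bearing at that visit. Because values are not replaced, the later tables would describe mainly knees that never needed revision. This differs from ordinary loss to follow-up, since the knee is absent because of the outcome being tabulated.

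The Discussion expects material differences to show in the radiologic and retrieval analyses, and 1-, 5- and 10-year results are to be published. The reading is blinded, but the selection of knees left to be read is not protected: the surgeons know the material, so the propensity to revise could differ by arm.

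**Working it through.** **The plan's own figures.** There is no stated loosening or revision rate to reproduce. The only stated figure used here is the number of patients. With margin 10, SD 30, one-sided α 0.05 and 80% power:

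n per group = 2 × 30² × (1.645 + 0.842)² / 10² = 111.3, rounded up to 112, so 224 in total. 224 / 0.80 = 280 per implant variant, and two variants give 560. With 1:1 allocation that is 280 per material. The sample size reproduces, and this point does not touch it.

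**Frequency of loosening on the 10-year film.** Let p be the true 10-year risk of loosening and s the share of loosened knees revised before that film. Both are assumed. Ignoring deaths, drop-out and other revisions, the frequency among unrevised knees is

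observed = p(1 − s) / (1 − ps).

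| True p | s = 25% | s = 50% | s = 75% |
|---|---|---|---|
| 3% | 2.3% | 1.5% | 0.8% |
| 5% | 3.8% | 2.6% | 1.3% |
| 8% | 6.1% | 4.2% | 2.1% |

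The table keeps about 76%, 51% and 26% of the true frequency. With 280 knees and p = 5%, there are 14.0 loosened knees, of which 10.5, 7.0 or 3.5 remain to be seen on the 10-year film.

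**Contrast between arms (assumed values).**
- True 2% vs 4%, equal s: 1.51% vs 3.03% at s = 25%, 1.01% vs 2.04% at 50%, 0.51% vs 1.03% at 75%. The ratio stays near 2. The difference falls from 2.0 points to about 1.5, 1.0 and 0.5.
- True 4% vs 8%, s = 25% vs 75%: 3.03% vs 2.13%, so the order reverses.
- True 5% vs 5%, s = 25% vs 75%: 3.80% vs 1.30%, a difference of 2.5 points where none exists.

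**Number of knees involved.** Assume 3% to 8% all-cause revision. The retrieval series cited in the Background gives aseptic loosening as 17.5% to 25.4% of revisions. Then 280 × 0.03 × 0.175 = 1.5 and 280 × 0.08 × 0.254 = 5.7 knees per material. This is only an order of magnitude: that series had mean implantation times of 1.2 to 1.5 years and highly crosslinked bearings, so it represents neither study material nor ten years of use.

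**Mean wear.** If wear is normal and the worst fraction r is removed, the mean falls by φ(c)/(1 − r) SD, with c the (1 − r) quantile. For r = 2%, 5% and 8% this is 0.05, 0.11 and 0.16 SD. This takes the removed knees to be exactly the most worn ones, and the shift is still small. Loosening frequency is the stronger ground.

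**The case against.** The strongest reply is that the harm is recorded elsewhere. A knee revised for loosening is a survival event with a documented reason, it can be counted among the categorized complications, and its bearing may be analyzed as a retrieval. That stands. A reader might infer that the trial as a whole under-reports harm from the bearing, and the documents do not support that. What remains is narrower: the survival curve mixes all causes and omits loosening seen on film without revision, and no stated analysis brings revision reasons and film findings together.

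A reader might also infer that the plan directs films of a replaced bearing to be scored as the original. It does not. That possibility follows from intent-to-treat with no rule on the matter, just as the loss of revised knees follows from the no-replacement rule.

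Loosening seen on an earlier film would be counted at that visit. That stands too, and the film schedule is in a table not shown. But visits fall at 5 and 10 years, so loosening that arises and is revised between them need not appear on any scheduled film.

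Finally, the secondary endpoints are exploratory ("whereas the secondary endpoints will be analyzed explorative"), and finer rules may sit in an analysis plan not shown. This lowers the severity. It does not remove the point, because the summary that is stated is the one that handles revised knees poorly.

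**Conclusion.** The point holds for the radiographic tables. As stated, frequencies and means without replacement would describe mainly unrevised knees at 5 and 10 years and would understate loosening. The size cannot be known from the documents. If 25% to 75% of loosened knees are revised first, roughly 75% to 25% of the true frequency remains visible.

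It is tempting to say that the bias always makes the materials look more alike. That is true of the absolute difference when the revised share is equal in both arms, but the ratio is then roughly kept. If revision thresholds differ by arm, the distortion can go either way. Neither the primary analysis nor the sample size is affected. Severity is minor to moderate.

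**What to change.** In the statistical analysis text, keep the visit tables and the all-cause survival curve, and add:

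- By arm, the 10-year cumulative incidence of radiographic loosening or bearing wear or fracture on any scheduled or pre-revision film, or revision with loosening or wear as the documented reason. The first of these sets the event date. Death and revision for other reasons are competing events.
- The blinded film component and the site-recorded revision component shown separately, so that the combined figure does not hide which part rests on unblinded judgement.
- A statement that films taken after exchange of the bearing or components are not scored as the allocated bearing.
- Each revised knee's last film with the original components in place, and any retrieval wear result, reported alongside the wear table. Do not convert these to a constant yearly wear rate, because the Discussion names creep separately from wear.

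The cost is some wording and a little programming. Films, revision reasons and revision dates are already collected, and no visits, readings or patients are added. Two limits remain: the revision reason comes from sites that know the material, and film-detected events are dated only to the visit. Last patient out is expected in Q4 2033, so the rule can be fixed well before the 10-year data are analyzed.

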## Discussion

The advancement of UHMWPE as a bearing material in the past 60 years can be considered as an evolution, adjusting the characteristics of the material to the function of the devices. Wear resistance, mechanical strength, oxidative stability, and the size of released particles are critical parameters influencing the safety and performance of the devices. MXE reveals a beneficial balance between these parameters and showed improved biomechanical properties in vitro in comparison to other established bearing materials. The comparison between MXE and ß-PE in this study will provide clinical data to confirm the biomechanical results in vivo.

It is assumed that material-related differences will be obtained, i.e., that the new material will be less sensitive to wear and creep. This may become obvious in radiologic analyses, where a new approach will be employed to measure wear of prosthesis components in situ [36, 33] and in biomechanical analyses of retrieved implants from revised patients. Whether these differences will lead to better clinical and functional outcomes or less complications and higher survival is in question and will be investigated thoroughly.

This study protocol features the history of development in knee arthroplasty technology from basic material sciences through biotribology and a final device to certification and application in humans. Through this study, data required by biomechanical testing can be confirmed or refuted, depending on whether there will be an advantage of the new material or not. This again may add knowledge to development and testing methods.

An apparent strength of this study is the comparison of two devices which only differ in their material but not in shape, dimensions, application, or other aspects. In combination with the new approach for the radiologic analysis to measure wear of prosthesis components in situ, the study performed according to this protocol is expected to deliver relevant results in the field of knee arthroplasty and implant technology.

## Trial status

This manuscript corresponds to version 1 of the approved study protocol. The study started in February 2021 with first patient in on 8 March 2021. To date (May 2023), 435 patients are included in the study. Last patient in is expected in December 2023, and, therefore, last patient out is expected in Q4 2033. Interim analyses will be performed as discussed above.

## Data Availability

Any data required to support the protocol can be supplied on request.

## Abbreviations

AS: Advanced surface
ASA: American Society of Anesthesiologists
ß-PE: ß-sterilized UHMWPE
EQ-5D-5L: 5-Dimensions 5-level measure of the EuroQol Group
fKSS: Knee Society Score function
kKSS: Knee Society Score knee
KSS: Knee Society Score
MXE: Medium crosslinked vitamin E-enriched UHMWPE
OKS: Oxford Knee Score
TKA: Total knee arthroplasty
UHMWPE: Ultra-high molecular weight polyethylene
